## Abstract

*Background*. Coronary heart disease (CHD) due to atherosclerotic inflammation remains a significant threat to global health despite the success of the lipid-lowering, anti-inflammatory statins. Tanshinone IIA, a potent anti-inflammatory compound derived from Traditional Chinese Medicine (TCM), may be able to supplement statins by further reducing levels of circulating inflammatory markers correlated to cardiovascular risk. Here, we present the protocol of a randomized controlled trial (RCT) that will investigate the synergistic effect of sodium tanshinone IIA sulfate and simvastatin on reducing elevated inflammatory markers in patients with CHD. Participants: Seventy-two inpatients with confirmed CHD, elevated serum high-sensitivity C-reactive protein (Hs-CRP) level, and a TCM diagnosis of blood stasis syndrome will be enrolled and randomized 1 : 1 into the control or experimental group. *Intervention*. All subjects will receive a standard Western therapy including 20 mg simvastatin orally once per evening. Patients in the experimental group will additionally receive a daily 80 mg dose of sodium tanshinone IIA sulfate intravenously, diluted into 250 mL 0.9% NaCl solution. The treatment period will be 14 days. *Outcomes*. Primary outcome parameter: serum Hs-CRP level. Secondary outcome parameters: other circulating inflammatory markers (including IL-6, TNF**α**, VCAM-1, CD40, sCD40L, MCP-1, and MMP-9), improvement in symptoms of angina and blood stasis syndrome, and safety. This trial is registered with ChiCTR-TRC-12002361.

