The danshen root contains tanshinone IIA, an active biochemical compound that has been shown to possess a multitude of antiatherosclerotic properties [8]. Most noteworthy is the ability of tanshinone IIA to decrease the levels of numerous inflammatory mediators associated with the progression of atherosclerosis, such as CRP, interleukin-6 (IL-6), tumor necrosis factor alpha (TNF*α*), vascular cell adhesion molecule-1 (VCAM-1), CD40, monocyte chemotactic protein-1 (MCP-1), and matrix metalloproteinase-9 (MMP-9) [8, 9]. A recent clinical trial demonstrated that giving simvastatin in combination with intravenous sodium tanshinone IIA sulfate (STS), the most widely used clinical formulation of tanshinone IIA in China, significantly decreased the levels of CRP, cholesterol, and plaque buildup in patients with peripheral vascular disease [10]. Notably, the integrative therapy was safer and more effective in treating this form of atherosclerosis than simvastatin alone. Whether there is potential for synergy between STS and statins in treating CHD, however, remains unknown.

Here, we present the protocol for a randomized, controlled clinical study that applies East-West integrative medicine to the treatment of CHD. Using standard Western therapy involving simvastatin as a foundation, we aim to explore the potential of further dampening the atherosclerotic inflammatory reaction in CHD-BSS patients through the concomitant addition of STS, utilizing the compound's potent anti-inflammatory properties as a supplement to simvastatin. In addition, we also aim to assess the integrative therapy's safety and its efficacy in improving angina and BSS symptoms relative to the simvastatin regimen without STS. Overall, this study offers an entry point for understanding and verifying the clinical applications of STS-statin integrative therapy in treating patients with CHD. 

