## 2. Methods/Design

### 2.1. Setting and Design

This trial is a monocentric, parallel-design, randomized, controlled, clinical pilot study that will be conducted at Xiyuan Hospital, and China Academy of Chinese Medical Sciences in Beijing, China. Subject recruitment is scheduled to begin in August 2012. This study will involve 72 patients with the diagnoses of CHD and BSS according to Western medicine and TCM, respectively. The 72 participants will be randomized 1 : 1 into a standard Western therapy (control) group and an East-West integrative therapy (experimental) group. For 14 days, all 72 patients will be treated with a standard Western therapy involving simvastatin, and patients in the experimental group will additionally receive intravenous STS. Data will be collected before initiating treatment, immediately after the 14-day treatment period and 30 days posttreatment. Serum CRP levels measured by high-sensitivity CRP (hsCRP) testing will serve as the primary outcome parameter, whereas the levels of other inflammatory markers, the improvement of angina and BSS symptoms, and safety will serve as secondary outcome parameters.

The study design is illustrated in Figure 1 and described in detail below according to the CONSORT 2010 statement [11].

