It is possible that the biomarker concentrations measured in our study may reflect systemic inflammation due to a cause other than atherosclerosis. Indeed, CRP is an acute phase protein released by the liver as part of the body's immune response to nonspecific disturbances, including infection, autoimmune disorders, trauma or surgery, and cancer [34]. To diminish the effect of this possibility, we will carefully consider the past and present medical histories of all eligible patients before enrollment and exclude any patients in whom inflammatory markers may not accurately reflect the state of CHD. Additionally, we will also monitor all study participants during the course of the trial for changes that may confound interpretation of biomarker data, such as acquisition of a nosocomial infection. 

The mechanisms by which tanshinone IIA and statins inhibit the inflammatory process of atherosclerosis are diverse, numerous, and in many cases shared (reviewed in [8, 35]). Using STS and simvastatin in combination may yield an additive, supplementary effect not only in the reduction of internal inflammation but also in the improvement of external symptoms associated with CHD. In this trial, we will examine the therapeutic efficacy of a STS-simvastatin integrative therapy in CHD patients by quantitatively scoring each study participant's angina and BSS symptoms and examining for any changes over the course of the trial. 

There is a risk for negative interactions in any combination drug therapy, but integrative treatments involving STS appear to be relatively safe. In a systematic review of 25 randomized controlled trials, Qiu et al. found that integrative therapies involving STS for unstable angina may produce fewer side effects than the component Western therapies alone [36]. Side effects that were associated with the integrative therapies included flushing, dizziness, bruising, gum bleeding, blood in the sputum, and swelling at the STS injection site, but none were considered severe and none resulted in discontinuation of treatment. Another clinical study, which used STS and simvastatin in combination to treat peripheral vascular disease also found the integrative treatment to be safer than the statin therapy alone [10]. Our study will continue to monitor the short- and long-term side effects of STS-simvastatin integrative therapy and verify the safety observations reported by previous trials.

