Several limitations affect the strength of our study design. Due to the unavailability of data needed to perform an *a priori* calculation, we determined the sample size for this study by adopting the number used in a comparable trial that we previously completed [14]. As a result, it is possible that our current study design may have insufficient power to reveal statistical significance at the level we desire. In addition, because the color of the STS solution makes double-blinding difficult, our study will be subjected to potential expectation biases from both clinical researchers and study participants. We will attempt to minimize these biases by maintaining blinding at the patient level to the fullest extent possible and by having clinical researchers interact with all subjects as similarly as possible. Full blinding will be maintained at the data analysis level. Finally, our project represents a single-center study and our results may not be wholly generalizable due to a possible selection bias. In the future, multicenter double-blinded, randomized controlled trials are necessary in order to faithfully establish the potential of STS-statin integrative therapy in treating CHD.

Nevertheless, the results of this trial are expected to clarify the potential of an East-West integrative therapy involving STS and simvastatin in reducing atherosclerotic inflammation in CHD patients. Our results will additionally confirm the safety and efficacy of this integrative therapy in treating CHD. Finally, the protocol of our study will also provide a methodological foundation upon which future clinical studies of integrative medicine may develop. 

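### The two arms can estimate the effect of adding STS to simvastatin but not synergy, and this pilot cannot confirm safety and efficacy as Section 3 says it will

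*Protocol article*

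**What the plan says.** **Aim.** The abstract of the protocol article presents a trial that "will investigate the synergistic effect of sodium tanshinone IIA sulfate and simvastatin on reducing elevated inflammatory markers in patients with CHD". Section 1 (Background) names the gap in knowledge in the same terms: "Whether there is potential for synergy between STS and statins in treating CHD, however, remains unknown". The next paragraph of Section 1 words the aim differently: "we aim to explore the potential of further dampening the atherosclerotic inflammatory reaction in CHD-BSS patients through the concomitant addition of STS". Section 3 (Discussion) is different again: "Using STS and simvastatin in combination may yield an additive, supplementary effect".

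**Design.** Section 2.1 says "This trial is a monocentric, parallel-design, randomized, controlled, clinical pilot study" and "The 72 participants will be randomized 1 : 1 into a standard Western therapy (control) group and an East-West integrative therapy (experimental) group". Sections 2.1 and 2.7 give simvastatin to both groups; STS is the only planned difference. Section 2.11 specifies two-group tests.

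**Announced conclusion.** The last paragraph of Section 3 before the Trial Status says: "Our results will additionally confirm the safety and efficacy of this integrative therapy in treating CHD". The paragraph before it lists the limitations: no data for a sample size calculation, possibly too little power, incomplete blinding and a single centre. It adds that double-blind trials in several centres will be needed.

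**The concern.** Synergy has a definite meaning: the two drugs together do more than their separate effects would add up to. A claim about it needs information on what STS does without simvastatin. Here STS is given only on top of simvastatin, so the abstract names a quantity that the design does not contain. *Additive* in Section 3 and *synergistic* in the abstract are different hypotheses, and the trial cannot choose between them.

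The second strand is the word *confirm*. A single-centre pilot without a power calculation, with a biomarker as primary outcome, gives preliminary evidence. Announcing confirmation before the data are in contradicts the limitations just before it.

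At stake is how the result may be read. A lower hsCRP in the STS arm could be taken as evidence of synergy, and a quiet safety record as proof of safety. The design supports neither.

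**Working it through.** **Inputs.** Two arms, 1:1, 72 patients (Section 2.1). Base size of 60, 30 per arm, and 20% dropout (Section 2.4). Two-sided 0.05 (Section 2.11). No SD, effect size or event rate is given, so the effect sizes and event rate below are assumptions.

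**The plan's own figure.** 60 × 1.2 = 72, hence 36 per arm. (Keeping 60 completers after 20% dropout would take 60 / 0.8 = 75. That is a separate matter and nothing here rests on it.) With 20% dropout, 36 × 0.8 = 28.8 per arm; 28 is used below as the rounded-down case.

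**Synergy.** Write the mean outcome as m00 (neither drug), mS (simvastatin only), mT (STS only) and mST (both), all on the same background care.

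- STS effect without simvastatin: τ = mT − m00.
- Departure from additivity: γ = (mST − mS) − (mT − m00).
- What the trial observes: δ = mST − mS = τ + γ.

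This is one equation with two unknowns. The pairs (τ = δ, γ = 0), (τ = 0, γ = δ) and (τ = 2δ, γ = −δ) mean respectively pure addition, pure synergy and antagonism, and all three give the same data. A larger sample narrows the interval for δ and says nothing about γ. The change from baseline does not help: Section 2.3 requires at least one month of prior statin use, so the baseline is not statin-free.

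**Efficacy, for scale.** Detectable standardized difference at 80% power = (1.960 + 0.842) × √(2/n).

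| n per arm | Detectable difference | Power for an assumed 0.5 SD |
|---|---|---|
| 36 | 0.66 SD | 56% |
| 30 | 0.72 SD | 49% |
| 28 | 0.75 SD | 46% |

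A large add-on effect on hsCRP could be detected. That would be a biomarker result from one centre, short of confirmed efficacy in CHD.

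**Safety, for scale.** With no events among n patients, the one-sided 95% upper bound is 1 − 0.05^(1/n).

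- n = 36: 1 − 0.05^(1/36) = 8.0%.
- n = 28: 1 − 0.05^(1/28) = 10.1%. This applies only if safety were judged in completers alone, and the article defines no such set.

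If the true risk of an event were 1% (assumed), the chance of seeing at least one among 36 is 1 − 0.99^36 = 30%.

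**Section 3 against the rest.** The study is a pilot (2.1), its size is borrowed because the data for a calculation were lacking (2.4), and Section 3 says that power may be too low and that further trials are necessary. The claim of confirmation cannot stand beside these statements.

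**The case against.** The strongest reply is that the document mostly describes itself correctly. The abstract promises to investigate synergy, not to demonstrate it, and its preceding sentence speaks of supplementing statins. The aims in Section 1 are exploratory and framed as the addition of STS, with safety and symptoms assessed against the regimen without STS. Section 2.11 plans no synergy test. *Confirm* is one sentence of expectation in the Discussion, and the limitations are stated openly.

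Most of this stands, and it narrows the point to wording. It does not remove it: a quantity that cannot be estimated cannot be investigated either, and the abstract does not match the aims in Section 1.

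Several stronger readings are tempting, and the documents do not support them:

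- *The formal aims are to show synergy and confirm safety.* The aims in Section 1 say neither.
- *Safety is not followed up at Phase III.* Table 1 schedules no routine blood, liver, kidney or coagulation tests and no electrocardiogram then, but it does tick a safety evaluation. Section 2.8 adds reported side effects and monitoring for serious events, and the laboratory tests are repeated at the end of treatment.
- *The follow-up claim is false.* Section 3 says "Our study will continue to monitor the short- and long-term side effects of STS-simvastatin integrative therapy", and follow-up ends 30 days after a 14-day course, about Day 44. Whether that is long-term is a matter of terminology.
- *A positive result will be reported as synergy.* That is a prediction, and Section 3 itself expects an additive effect.

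An article also need not print a hypothetical zero-event bound. The 8.0% is given here only for scale.

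**Conclusion.** The point holds as a correction of stated claims. The synergy part is structural: the only identifiable contrast is the effect of adding STS, on any outcome scale and at any sample size. It rests on synergy meaning a departure from additivity. If the word was meant loosely, as extra benefit, it should still go, because Section 1 and Section 3 already describe that benefit in add-on terms. The confirmation part is an internal contradiction, and the figures show its size: a zero-event bound of 8.0% at 36 STS patients and a detectable hsCRP difference of 0.66 SD at 36 per arm.

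A reader might infer that the design fails or that arms must be added. It does not follow. The add-on question is answerable with the arms as planned, and Section 2.6 states that nobody will be denied standard therapy.

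**What to change.** - **Abstract:** replace the reference to a synergistic effect by *the effect of adding STS to simvastatin-based standard therapy*. This matches the aims in Section 1.
- **Section 1:** align the sentence on synergy, for example by posing as the open question whether adding STS to a statin gives further benefit in CHD.
- **Section 3, last paragraph:** replace the promise of confirmation by *provide preliminary estimates, with 95% confidence intervals, of the effect on hsCRP and symptoms and of adverse-event rates*. Leave confirmation to the larger trials that the section already calls for.

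These are changes of wording. No arm, endpoint, sample size or test is affected. The downside is a more modest claim.

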## 1. Background

Cardiovascular disease is the worldwide leading cause of death. Globally in 2008, over 17 million people died from cardiovascular diseases, representing 30% of total deaths around the world [1]. Among all cardiovascular diseases, coronary heart disease (CHD) is responsible for the greatest mortality, accounting for 7.3 million deaths worldwide in 2008 [1]. 

CHD involves narrowing of the arteries supplying oxygen to the heart, most often due to buildup of atherosclerotic plaque in the coronary vessels. The ultimate rupture of atherosclerotic plaque may lead to the onset of acute coronary syndrome (ACS), a medically emergent manifestation of CHD involving unstable angina or myocardial infarction. 

The formation of atherosclerotic plaque is an inflammatory response, usually associated with elevated levels of low-density lipoprotein cholesterol (LDL-C) in the blood [2]. To this end, statins have served as a notably successful pharmacologic intervention against CHD from the standpoint of Western medicine. One meta-analysis study found that the average statin regimen reduces LDL-C levels by 35%, leading to a 60% decrease in ischemic cardiac events such as those of ACS [3]. Remarkably, as demonstrated by the PRINCE study, statins also moderate the atherosclerotic inflammatory response by reducing levels of C-reactive protein (CRP) [4], a robust marker of systemic inflammation whose concentration in the blood strongly correlates with the patient's cardiovascular risk [5]. Nevertheless, a multicenter study involving over 4,000 ACS patients showed that 22.4% of patients receiving intensive statin therapy suffered a serious cardiovascular or cerebrovascular event within two years of initiating treatment [6], indicating that although statins may be one of Western medicine's most effective agents for CHD, the toll of this disease remains significantly high.

At East-West integrative medical centers in Asia, cardiovascular diseases may also be evaluated according to the principles of Traditional Chinese Medicine (TCM). Among patients with the Western diagnosis of CHD, the TCM diagnosis of blood stasis syndrome (BSS) is exceedingly common, and the treatment for these CHD-BSS patients via TCM frequently involves herbal therapies using the root of *Salvia miltiorrhiza* (*丹参*, danshen) [7].

The danshen root contains tanshinone IIA, an active biochemical compound that has been shown to possess a multitude of antiatherosclerotic properties [8]. Most noteworthy is the ability of tanshinone IIA to decrease the levels of numerous inflammatory mediators associated with the progression of atherosclerosis, such as CRP, interleukin-6 (IL-6), tumor necrosis factor alpha (TNF*α*), vascular cell adhesion molecule-1 (VCAM-1), CD40, monocyte chemotactic protein-1 (MCP-1), and matrix metalloproteinase-9 (MMP-9) [8, 9]. A recent clinical trial demonstrated that giving simvastatin in combination with intravenous sodium tanshinone IIA sulfate (STS), the most widely used clinical formulation of tanshinone IIA in China, significantly decreased the levels of CRP, cholesterol, and plaque buildup in patients with peripheral vascular disease [10]. Notably, the integrative therapy was safer and more effective in treating this form of atherosclerosis than simvastatin alone. Whether there is potential for synergy between STS and statins in treating CHD, however, remains unknown.

Here, we present the protocol for a randomized, controlled clinical study that applies East-West integrative medicine to the treatment of CHD. Using standard Western therapy involving simvastatin as a foundation, we aim to explore the potential of further dampening the atherosclerotic inflammatory reaction in CHD-BSS patients through the concomitant addition of STS, utilizing the compound's potent anti-inflammatory properties as a supplement to simvastatin. In addition, we also aim to assess the integrative therapy's safety and its efficacy in improving angina and BSS symptoms relative to the simvastatin regimen without STS. Overall, this study offers an entry point for understanding and verifying the clinical applications of STS-statin integrative therapy in treating patients with CHD. 

## 2. Methods/Design

### 2.1. Setting and Design

This trial is a monocentric, parallel-design, randomized, controlled, clinical pilot study that will be conducted at Xiyuan Hospital, and China Academy of Chinese Medical Sciences in Beijing, China. Subject recruitment is scheduled to begin in August 2012. This study will involve 72 patients with the diagnoses of CHD and BSS according to Western medicine and TCM, respectively. The 72 participants will be randomized 1 : 1 into a standard Western therapy (control) group and an East-West integrative therapy (experimental) group. For 14 days, all 72 patients will be treated with a standard Western therapy involving simvastatin, and patients in the experimental group will additionally receive intravenous STS. Data will be collected before initiating treatment, immediately after the 14-day treatment period and 30 days posttreatment. Serum CRP levels measured by high-sensitivity CRP (hsCRP) testing will serve as the primary outcome parameter, whereas the levels of other inflammatory markers, the improvement of angina and BSS symptoms, and safety will serve as secondary outcome parameters.

The study design is illustrated in Figure 1 and described in detail below according to the CONSORT 2010 statement [11].

### 2.2. Diagnostic Criteria

The diagnosis of CHD will be based on the standardized criteria established in “Nomenclature and criteria for diagnosis of ischemic heart disease,” a joint report published by the International Society and Federation of Cardiology and the World Health Organization [12]. In addition, following the current practice of CHD clinical research, we will require subjects to either have a previous history of myocardial infarction or have at least one coronary artery stenosis ≥50% confirmed by coronary angiography in order to ensure the diagnosis of CHD. 

The TCM diagnosis of BSS will follow the principles described in “Criteria for TCM syndrome differentiation of patients with coronary heart disease,” published by the China Society of Integrated Traditional Chinese and Western Medicine [13].

### 2.3. Subject Inclusion and Exclusion

To participate in this study, subjects must be 35 to 75 years of age and must either have a previous history of myocardial infarction or have at least one coronary artery stenosis ≥50% confirmed by coronary angiography. In addition, subjects must currently be hospitalized with either unstable angina or an acute non-ST segment elevation myocardial infarction and have taken statin medicine for at least 1 month. From a TCM perspective, study participants must have the diagnosis of BSS. Finally, subjects must have a serum hsCRP level between 3 mg/L and 15 mg/L.

The criteria for exclusion include infection, fever, trauma, burn injury, or surgery within one month prior to recruitment; a concomitant diagnosis of cancer, sexually transmitted diseases, tuberculosis, or rheumatoid arthritis or other autoimmune diseases; or a history of serious pulmonary, hepatic, renal, neurological, psychiatric, or hematological diseases. In addition, subjects must not have previously undergone or currently be planning to undergo surgical intervention for CHD. Patients with severe heart failure indicated by an ejection fraction <35% will be excluded as will those with a reduced platelet count or a tendency to bleed or hemorrhage. Study participants must not currently be taking antibiotics or using TCM preparations that relieve fever or clear internal heat. Finally, patients who may become noncompliant or may participate in other clinical trials will be excluded.

During the course of the study, a subject may be excluded if (1) it is discovered that a subject was misdiagnosed for either BSS or CHD or was otherwise inappropriately accepted for participation in the trial; (2) if a subject misses a significant number of treatments or is missing significant records of data; (3) if subject's blood samples from the first two phases of the study (see Section 2.9) are contaminated or damaged in any way such that reliable data cannot be obtained; or (4) if for any reason (e.g., onset of a mid-study nosocomial infection), patient's inflammatory marker levels may not accurately reflect atherosclerotic inflammation. 

